#### Injuries and illness

The incidence and type of injury and illness of the participant at T0 and 3 months in retrospective will be filled out via a digital questionnaire and takes 5 min to complete. The injury density (ID) will be calculated per 1000 h of scheduled physical activity (van Mechelen et al. 1992).

Besides the retrospective registration, the injuries and illnesses will also be monitored longitudinal for 1 year, every 2 weeks. The parent and/or participant receives a short digital questionnaire of 5 simple questions, send by email and takes approximately 1 min to complete. If a question will be answered positively, there will be a telephone conversation with the child, young adult or parent, to detect the cause and severity to register the diagnosis of injury or illness. The researcher will register the injury by using a classification list. Only if the diagnosis remains unclear after the telephone conversation, a physical examination of a sports physician or a physical therapist will take place.

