**Methods:**

In this cross-sectional study differences will be compared in regards to physical and psychosocial health, cognitive functioning, school performance, daily physical activity and injuries between children and adolescents with a chronic disease or physical disability who participate in sports and those who do not. Children and adolescents, both ambulatory and wheelchair dependent, in the age of 10–19 years with a physical disability or chronic disease will be included. “Sports” is defined as participation in an organized sport at least two times a week for a duration of 3 months or more prior to the assessment. Parametric and non-parametric statistics will be used to determine the differences between the two groups.

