### Participants

Eligible for this study are all children and adolescents aged from 10 up to 19 years with a physical chronic disease or condition, including cardiovascular, pulmonary, musculoskeletal, metabolic or neuromuscular disorders. Table 1 shows the in- and exclusion criteria. Both children who are ambulatory or those propelling a wheelchair are eligible for this study. Participants have to understand the Dutch language, understand simple instructions and be able to perform a physical fitness test. Children and adolescents in electric wheelchair, having a progressive disease or participate in other research projects which might influence the current study results will be excluded. Contra-indications for performing an exercise test, based on the exercise pre-participation screening questionnaire, may lead to exclusion on the cardiopulmonary exercise test (Balady et al. 1998).

**Table 1 Tab1:** Eligibility and exclusion criteria

Eligibility	Exclusion
Children and adolescents with a physical disability or chronic disease: cardiovascular, pulmonary, musculoskeletal or neuromuscular disorder Children and adolescents between the age of 10 and 19 years Children and adolescents have to understand simple instructions Children and adolescents are able to perform physical fitness tests	Children and adolescents with progressive diseases Children and adolescents using an electric wheelchair During the length of the study, children are not allowed to participate in other research projects which might influence the current study results For the sporting group of the HAYS-study only: subjects who have not participated in any sports for the preceding 3 months No signed informed consent

Informed consent must be provided by all parents, as well as by subjects up from 12 years till 17 years. In line with Dutch law, no parental informed consent is required for subjects aged 18 years and over.

This study was approved by the Medical Ethics Committee of the University Medical Center Utrecht, the Netherlands.

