### Outcome measures

Table 3 shows an overview of the outcome measures and chosen measurement instruments in this study.

**Table 3 Tab3:** Overview of assessments used instruments, questionnaires and time schedule

Outcome measure	Parameter	Variable	Measurement	Time at location	Time at home
General	Demographics	DOB, Gender, Diagnosis, FMS score, activity level	General questionnaire		5 min
Cardiovascular health	Metabolic parameters	BMI	Height, Weight	5 min	
		Fat Free Mass	BIA		
		Blood pressure	Sphygmomanometer	10 min	
		Arterial stiffness Pulse wave velocity	Arteriograph		
Physical fitness	Aerobic fitness	VO_2peak_ RER Anaerobic threshold	CPET Shuttle run/ride test Bicycle test	30 min	
	Anaerobic fitness	Peak power Mean power	MPST	5 min	
	Muscle strength	Isometric muscle strength Explosive muscle strength	Grip strength Reverse curl Seated push up Standing broad jump or One stroke push	10 min	
	Flexibility		Modified Apley test Modified Thomas test	5 min	
	Agility		10 × 5 meter sprint	5 min	
Physical activity	Intensity	Heart rate	Actiheart	5 min	7 days
	Modality	Type of activity	Activ8 and Activity diary	5 min	7 days
Cognitive functioning	School performance	Educational level	Type of education Recent CITO-score	0 min	
	Attention	Focused attention Sustained attention Strategy Distractibility	Bourdon-Vos Cancellation task Capture task	15 min 5 min	
Injury and illness	Incidence injury and illness	Retrospective 3 months	Online questionnaire		3 min
		Longitudinal 1 year, every 2 weeks	Online questionnaire		
	Classification of injury or illness (if applicable)		Telephone conversation		5 min
Psychosocial health	Self-perception		Self-perception profile for children (SPPC)	10 min	
	Quality of life		Disabkids		10 min
	Self-efficacy		Exercise self-efficacy Scale		2 min
Total time				150 min	28 min

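### The twice-weekly sport definition and the retrospective injury and illness count cover the same 3 months, so under that definition an injury can decide group membership; Table 1 states a looser rule and the two are not reconciled

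*Protocol article*

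**What the plan says.** **Exposure.** The Abstract (Methods) defines sport as "participation in an organized sport at least two times a week for a duration of 3 months or more prior to the assessment". Table 1 (Participants) lists a different rule among its exclusions: "For the sporting group of the HAYS-study only: subjects who have not participated in any sports for the preceding 3 months". That rule names no frequency and does not ask for organized sport. It is the only criterion in the table that concerns sport history, and it applies to the sport group alone. The Design section describes the comparison group as peers who do not do sport, without saying over what period.

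**Outcome.** The section Injuries and illness collects "The incidence and type of injury and illness of the participant at T0 and 3 months in retrospective", and Table 3 lists the same item as "Retrospective 3 months". The same paragraph adds: "The injury density (ID) will be calculated per 1000 h of scheduled physical activity". A second source follows: "the injuries and illnesses will also be monitored longitudinal for 1 year, every 2 weeks".

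**Expectation.** The Discussion hypothesizes a lower incidence density in the group that does sport. It does not say whether the retrospective or the prospective data will test this.

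The article does not say how to classify a child who was doing sport and paused or stopped within the 3 months because of injury or illness.

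**The concern.** In a sound comparison of injury between sporting and non-sporting children, group membership does not depend on whether the child was injured. Here it can. If twice-weekly sport over the whole 3 months is the entry condition, a child injured in the middle of the window may fail it because of the very event being counted. The sport group then keeps children who had no injury, or only injuries they could play through.

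The stated aim covers negative as well as positive effects of sport, and the Background says that parents and healthcare providers worry about injuries that would limit the child further. Injuries serious enough to stop sport are the ones most likely to be lost. The distortion runs in the direction of the study's own hypothesis, so a favourable retrospective result could not be told apart from selection.

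**Working it through.** The plan gives no figure to reproduce on this point. The check compares the sections and then illustrates the size on assumed inputs.

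**1. The two windows.** Sport exposure: the 3 months or more before assessment (Abstract, Methods). Retrospective outcome: T0 and the 3 months before it (Injuries and illness; Table 3). They coincide.

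**2. A test case.** Take a child who did organized sport twice a week for a long time and stopped after an injury halfway through the window.
- Abstract definition: twice-weekly participation was not kept up over the 3 months, so the child can fail it.
- Table 1: the child did some sport in the window, so the child is not excluded from the sport group.
- Comparison group: no listed criterion excludes recent sport.

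The two criteria disagree about this child. Table 1 does not say that it replaces the definition. If both must be met, the stricter one decides.

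**3. Size under the Abstract definition.** All inputs are assumptions except the 73 per group, which is half of the planned 146.
- r = true injury rate per 1000 h, 1 to 5
- h = hours of sport a week, 2 to 4
- window = 13 weeks
- q = share of injuries that stop sport, 0.25 to 0.50

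Let injuries per child be Poisson with mean λ = r × 13h / 1000, and suppose that every child with a sport-stopping injury is excluded. The excluded children's hours leave with them. Those who remain contribute only non-stopping injuries, so:
- observed rate = r(1 − q)
- share of sporting children excluded = 1 − exp(−λq)

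Worked example, r = 2, h = 4, q = 0.50:
- λ = 2 × 52 / 1000 = 0.104
- observed rate = 2 × 0.50 = 1.0 per 1000 h, half of the true rate
- share excluded = 1 − exp(−0.052) = 5.1%, or 3.7 of 73

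Over the ranges:

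| q | observed / true rate | share excluded (lowest: r = 1, h = 2; highest: r = 5, h = 4) | of 73 |
|---|---|---|---|
| 0.25 | 75% | 0.6% to 6.3% | 0.5 to 4.6 |
| 0.50 | 50% | 1.3% to 12.2% | 0.9 to 8.9 |

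The relative bias depends only on q. Even when few children are lost, they carry a large part of the injuries.

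**4. Size under Table 1 alone.** Only a child out of sport for the entire 3 months is excluded. Such an absence must begin at or before the start of the window, so almost no injury arising within it is lost. The bias is close to nil.

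**5. The 1-year monitoring.** It runs forward after the groups are formed, so an injury counted there cannot have decided the group.

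**The case against.** The strongest reply is that the article nowhere demands sport without a break. A reader might infer from the Abstract that any pause disqualifies a child and that injured children are therefore removed. The text does not say so: it is silent on short absences, and Table 1 would keep most such children. This stands, and it limits the point to a bias that can arise under one of two stated criteria.

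A reader might also infer that injured sporters are enrolled as controls, which would raise the comparison group's count and widen the gap. No section sends them there, and the Design section's description of the comparison group argues against it. All that can be said is that no criterion prevents it. Calculations that assume such a transfer, or that use the percentage of children injured instead of the planned density per 1000 h, should not carry the size of this point.

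Both groups must also meet "Children and adolescents are able to perform physical fitness tests". A child still unable to do the tests is therefore lost from either group. This does not help with a child who has recovered but missed weeks of sport.

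A rule for brief interruptions might be left to the full protocol. But the article itself prints two differing exposure criteria and an overlapping outcome window. Children turned away or misallocated at enrolment cannot be recovered by a later analysis plan.

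Finally, injury is one of many outcomes, the sample size rests on peak oxygen uptake, and prospective injury data are already planned. That keeps the point moderate; it does not remove it.

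**Conclusion.** The point holds in limited form. Under the Abstract's definition, an injury or illness within the 3 months can cost a child sport-group status, and the retrospective comparison can then favour sport. If all children with a sport-stopping injury are excluded, the observed sport-group rate is 75% to 50% of the true rate for an assumed q of 0.25 to 0.50. Under Table 1 alone the bias is close to nil. The article does not settle which criterion applies, and it gives neither injury rates nor the share of injuries that stop sport, so these figures are a range under assumptions and not an estimate.

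It would go too far to conclude that the study's injury findings as a whole will make sport look safer. The overlap affects only the retrospective count. The 1-year monitoring is free of it, although it too may enrol mainly children who tolerate sport.

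**What to change.** 1. Reconcile the sport definition in the Abstract with the Table 1 exclusion, so that one criterion governs entry to the sport group.
2. State that a child whose sport was interrupted by injury or illness within the 3 months is classified by usual participation before the event.
3. Name the planned 1-year prospective follow-up, with group fixed at T0, as the basis for the sport versus non-sport comparison of injury and illness.
4. Report the retrospective 3-month data descriptively.

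The cost is a few sentences in the exposure definition and the analysis section, with no new data collection. The price is that the retrospective data no longer support a comparison between groups.

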#### School performance

The type of education of the participant will be noted. If available, outcomes of a national educational achievement test (CITO) will be used for quantifying school performance, in both ‘elementary school’ and ‘secondary school’.

#### Cognition

To evaluate cognitive functioning, attention will be measured. To overcome locomotive influences attention tests will be carried out on a tablet (Asus Eee Slate Tablet, with a 12.1 inch display and clock speed of 1.33 GHz).

Three types of attention will be measured: sustained attention, search strategy and distractibility. Sustained attention will be measured using an adapted digitalized version of the Bourdon-Vos task (Vos 1992). This task is a time-limited test. Children had to continue until the whole test was finished, or stop after 10 min. For distractibility an object cancellation task will be used and takes 5 min to complete. The search strategy of the participant during this cancellation test for distractibility is computed afterwards via software of this tablet test. Another test for measuring distractibility is the capture task. This test was adapted from Van Der Stigchel and Nijboer (2010). In each trial the participant is asked to focus on a central fixation cross. When the cross disappears, the target, represented as an apple, appears in one of the corners. In 50 % of the trials, a distractor will appear as well. Reaction time will be measured for both conditions to calculate distractibility.

#### Psychosocial health

To evaluate self-perception in this study, the Dutch translation of the self-perception profile scale (SPPS) for children and for adolescents will be used (Harter S 1985). This questionnaire has been validated to measure self-perception. The questionnaire will take approximately 10 min to complete.

#### Quality of life

To evaluate the quality of life satisfaction, the Dutch version of the Disabkids will be used. This questionnaire measures the quality of life and the independence of children with chronic health conditions. It takes approximately 10 min to fill out.

#### Self-efficacy

To assess self-efficacy specific for exercise and physical activity a Dutch questionnaire is filled out digitally at home by the child and will take approximately 2 min (Nooijen et al. 2013).

## Sample size

The sample size of the HAYS-study is based on a study of Verschuren and Takken (2010). In this study children and adolescents with cerebral palsy had an average peak oxygen uptake of 42 ± 8.2 ml/kg/min. To prove a difference of 10 % between sporting or non-sporting subjects, with an alpha of 0.05 and bèta of 0.20 (power of 0.80) a sample size of 66 subjects per group is required. When taking a failure rate of 10 % into account, 146 subjects should be included in total.

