## Discussion

The current paper describes the rationale, design and methods of a cross-sectional study concerning participation in sports focused on children and adolescents with a physical disability or chronic disease.

To our knowledge this is the first study to evaluate this effect of sport participation on physical, social and mental health within this population. The aim is to determine both the positive and negative effects of sports related to health outcomes in children with disabilities and chronic childhood onset conditions. We hypothesize that the group participating in sports regularly will show higher levels of physical activity associated with better health outcomes, a relative lower incidence density, better cognitive functioning and school performance.

New insights gained from this study could stimulate the improvement of facilities for adapted sports by the government. Also children with a chronic disease or physical disability and their caregivers, sport coaches, physical therapists and other interested parties will be more easily convinced of the advantages of sports participation for this population.

Although we carefully chose our study settings according to its population, we are aware of some limitations of the study.

Objective measurements are chosen where possible. To achieve the best results possible, the best fitting testing modality will be chosen for each participant. The testing modality has to mimic the type of sport participated in. In children who do not participate in sport, the most common form of physical activity in daily life will be chosen as an indicator for the test modality. In general, some test modalities have been proven to elicit a higher VO_2_ peak in the same subject (Bhambhani et al. 1992). The test modality could therefore influence the test outcome. To minimalize this bias we will pursue a comparable number of testing modality types in both groups.

In conclusion, this study will provide insight in the effects of sports participation on the health of children and adolescents with a chronic disease or physical disability.

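### The planning mean and SD for VO₂peak come from cerebral palsy only, so the 80% power for a 10% difference is not justified for the mixed population under an independent-samples test

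*Protocol article*

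**What the plan says.** The Sample size section of the protocol article takes its planning values from a single published study: "In this study children and adolescents with cerebral palsy had an average peak oxygen uptake of 42 ± 8.2 ml/kg/min". The target is stated as "To prove a difference of 10 % between sporting or non-sporting subjects", "with an alpha of 0.05" and power 0.80, and the conclusion is that "66 subjects per group is required". A 10% failure allowance brings the total to 146. The section gives no reason why the cerebral palsy figures should hold for the study population, and no range of alternatives.

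The Participants section admits physical chronic conditions "including cardiovascular, pulmonary, musculoskeletal, metabolic or neuromuscular disorders". That is five groups; Table 1 lists four and omits metabolic. The same section says: "Both children who are ambulatory or those propelling a wheelchair are eligible for this study". Table 4 grades ambulatory subjects from those who cannot walk 400 m in 6 minutes to those used to running at 8 km/h in their sport. The Aerobic fitness section measures VO₂peak by shuttle run, shuttle ride or cycling. The Discussion concedes that "some test modalities have been proven to elicit a higher VO"₂peak in the same subject.

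The Design section matches sporting and non-sporting subjects on gender, age and diagnosis. The Statistical analysis section names only independent-sample t-tests or non-parametric equivalents for the group comparison.

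**The concern.** Power for a difference in means depends on the SD that enters the test. Here that is the SD of VO₂peak across everyone in a group, because an independent-samples test removes nothing for diagnosis, age, gender or mode of locomotion. An SD from one diagnosis is the right input only if it also describes the spread in the mixed group, and the article does not argue that it does. The mean matters as well, because the target is a percentage: 10% of 42 is 4.2 ml/kg/min, and a different mean gives a different target.

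If the mixed-population SD is larger than 8.2, a VO₂peak comparison that finds no difference will be less informative than the stated power suggests. The reader of the article has no means of judging by how much.

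**Working it through.** **Inputs from the Sample size section.** Mean 42, SD 8.2, difference 10% × 42 = 4.2 ml/kg/min, alpha 0.05 (two-sided assumed; the article does not say), power 0.80, equal groups.

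**The plan's own figure.** The normal approximation is n per group = 2 (1.960 + 0.842)² × SD² / difference². With the stated inputs this is 2 × 7.849 × 67.24 / 17.64 = 59.8, so 60 per group. The exact t-test gives 61 and a one-sided test 48. None of these is 66. If the difference is rounded to 4.0, the normal approximation gives 66, but the article does not state that step. The total follows from 132 × 1.1 = 145.2, rounded up to 146. So 66 per group carries a little slack: under the stated inputs its power is 0.83.

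**How far the slack reaches.** With 66 per group, the standardised difference detectable with 80% power (t-test) is 0.491. For a difference of 4.2 this corresponds to SD = 4.2 / 0.491 ≈ 8.55.

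**Power and detectable difference over a range of SDs** (66 per group, two-sided 0.05, t-test; SDs above 8.2 are assumptions):

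| SD | Power for 4.2 | Detectable difference at 80% power (0.491 × SD) |
|---|---|---|
| 8.2 | 0.83 | 4.0 |
| 8.5 | 0.80 | 4.2 |
| 9 | 0.76 | 4.4 |
| 10 | 0.67 | 4.9 |

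These figures treat the two groups as independent samples, as the planned test does. The documents give no value for the correlation that matching may induce.

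**What mixing can do, by assumption.** If a share p of subjects has a mean that differs by D from the rest, and each part has within-part SD s, the overall SD is √(s² + p(1 − p)D²) and the overall mean shifts by pD. With p = 0.2, and power for a difference of 10% of the resulting mean:

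| Within-part SD | Shift D | Overall SD | Overall mean | Power |
|---|---|---|---|---|
| 8.2 | 5 lower | 8.4 | 41 | 0.79 |
| 8.2 | 5 higher | 8.4 | 43 | 0.83 |
| 8.2 | 10 lower | 9.1 | 40 | 0.71 |
| 8.2 | 10 higher | 9.1 | 44 | 0.79 |
| 7 | 10 lower | 8.1 | 40 | 0.81 |

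None of these inputs is in the documents. The rows show that power may stay near 0.80 or fall clearly below it, depending on values the article does not give.

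**What adjustment recovers in the same example.** With s = 8.2 and D = 10, an unadjusted test works with SD 9.1 and has power 0.75 for a difference of 4.2. A comparison within the two parts works with SD 8.2 and has about 0.83.

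**The case against.** A reader might infer that the study has less than 80% power, or that pooling these diagnoses must lower the mean and widen the SD. The documents do not support that. They give no VO₂peak mean or SD for any other eligible diagnosis, for wheelchair users or for cyclists. The Recruitment section reaches up to high-level competitive athletes, so the mixed mean could exceed 42. Pooling pushes the SD above 8.2 only if the within-subgroup SDs are not correspondingly smaller. The planning sample may itself have included varied mobility: the article describes wheelchair tests in youth with cerebral palsy and does not say who was in the source study. The 66 per group also absorbs modest extra spread. All of this stands, and it is why the point concerns justification and not a demonstrated shortfall.

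A second objection is that the design already deals with heterogeneity, through matching and through the stated aim of similar numbers of each test modality in both groups. These steps limit imbalance and hence bias. They do not take between-diagnosis or between-locomotion variance out of the error term of an independent-samples test.

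A third is that borrowing an SD from one published study is common, and that a condensed article may leave the reasoning to the full protocol. That tempers the criticism. Even so, the source, the SD, the effect and the power are all printed, and the source population is visibly narrower than the eligible one.

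Finally, nothing in the article says that a null result would be read as excluding a 10% difference. That risk is possible but is not a stated intention.

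**Conclusion.** The concern holds in a limited form. The planning values come from cerebral palsy only and are not shown to apply to the eligible mix of diagnoses, walkers and wheelchair users. The 80% power for a 10% difference is therefore not justified for that population under the named test. Neither the direction nor the size of any error can be derived from the documents.

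On the plan's own inputs, 66 per group gives 0.83, and about 80% is kept up to an SD of roughly 8.5. Beyond that the loss is material: 0.76 at SD 9 and 0.67 at SD 10 for a difference of 4.2. These results assume a two-sided 0.05 t-test, independent groups and a fixed difference of 4.2. The SDs above 8.2 are illustrations, not estimates.

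**What to change.** Leave enrolment and the test procedures as they are, and make two changes.

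1. **Analysis.** Compare VO₂peak between the sport and non-sport groups with a model adjusted for, or stratified by, locomotion group (wheelchair or ambulatory, as already assigned from the FMS at 500 m in the Physical fitness section) and the matching factors gender, age and diagnosis. The residual within-stratum SD then governs precision, and the matching is used in the analysis. Keep run/cycle modality for a sensitivity analysis only. The Discussion lets the sport practised determine the modality, so it is partly a consequence of the exposure, and conditioning on it in the main comparison is debatable.

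2. **Sample size text.** State that 42 ± 8.2 is from cerebral palsy only. Replace the unqualified 80% claim with power or detectable difference over a range of SDs, for example 8.2 to 10 as tabulated above.

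All the variables are already collected. The cost is slightly more analysis work and a stated power that may be less favourable.
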